## Abstract

**Background:**

Postoperative morbidity and mortality in patients undergoing surgery is high, especially in patients who are at risk of complications and undergoing major surgery. We hypothesize that perioperative, algorithm-driven, hemodynamic therapy based on individualized fluid status and cardiac output optimization is able to reduce mortality and postoperative moderate and severe complications as a major determinant of the patients’ postoperative quality of life, as well as health care costs.

**Methods/design:**

This is a multi-center, international, prospective, randomized trial in 380 patients undergoing major abdominal surgery including visceral, urological, and gynecological operations. Eligible patients will be randomly allocated to two treatment arms within the participating centers. Patients of the intervention group will be treated perioperatively following a specific hemodynamic therapy algorithm based on pulse-pressure variation (PPV) and individualized optimization of cardiac output assessed by pulse-contour analysis (ProAQT© device; Pulsion Medical Systems, Feldkirchen, Germany). Patients in the control group will be treated according to standard local care based on established basic hemodynamic treatment. The primary endpoint is a composite comprising the occurrence of moderate or severe postoperative complications or death within 28 days post surgery. Secondary endpoints are: (1) the number of moderate and severe postoperative complications in total, per patient and for each individual complication; (2) the occurrence of at least one of these complications on days 1, 3, 5, 7, and 28 in total and for every complication; (3) the days alive and free of mechanical ventilation, vasopressor therapy and renal replacement therapy, length of intensive care unit, and hospital stay at day 7 and day 28; and (4) mortality and quality of life, assessed by the EQ-5D-5L™ questionnaire, after 6 months.

**Discussion:**

This is a large, international randomized controlled study evaluating the effect of perioperative, individualized, algorithm-driven ,hemodynamic optimization on postoperative morbidity and mortality.

**Trial registration:**

Trial registration: NCT03021525. Registered on 12 January 2017.

**Electronic supplementary material:**

The online version of this article (10.1186/s13063-018-2620-9) contains supplementary material, which is available to authorized users.

## Background

In high-risk surgical patients, rates of postoperative complications range from 25% up to more than 40% [1, 2]. These patients not only have reduced functional independence, quality of life and long-term survival [3, 4], moreover, the treatment of postsurgical complications is extremely expensive. In the US the average extra cost for treating a patient developing one or more complication is approximately US$18,000 [1, 5, 6]. Therefore, reduction of postsurgical complications with fewer days in an intensive care unit, fewer days on organ support, reduction of resource utilization and reduction of hospital stay would reduce costs also for the health care system. Inadequate supply of oxygen is one of the major factors leading to postoperative organ dysfunction and complications. Oxygen supply is mainly determined by cardiac output rather than blood pressure, which, however, has been the primary hemodynamic target during surgery for decades and still is. In this context hemodynamic goal-directed therapy, focusing on an optimization of fluid status and cardiac output, is believed to have the ability to reduce postoperative complications. Since methods like thermodilution, arterial pulse-contour analysis or esophageal Doppler allow routine measurement of cardiac output, several single-center studies have brought up the first evidence that perioperative, algorithm-driven optimization of cardiac output can reduce postoperative complications and improve outcome [7–11]. Also meta-analyses have demonstrated a reduction of morbidity in patients undergoing high-risk surgery [12–17]. However, comparability of those studies is limited due to inhomogeneity in population and therapeutic approaches. Moreover, in most published trials so far, hemodynamic goals had been predefined independently from the individual need of the single patient and further generalized to an entire study population, i.e., either dedicated values of stroke volume or cardiac output, or a standardized maximization of stroke volume by volume loading were used for all patients.

The focus in previous studies was put on implementation of fixed values of hemodynamic parameters, disregarding the single patient’s individual cardiovascular capacities, especially the individual range of cardiac output.

The hypothesis of the planned clinical trial is that perioperative hemodynamic optimization based on the novel approach of individualization of hemodynamic therapy can reduce postoperative morbidity and mortality.

## Methods/design

### Justification of the study

The present study aims to evaluate the impact of perioperative, algorithm-driven, hemodynamic therapy based on individualized fluid status and individualized cardiac output optimization on postoperative moderate and severe complications and mortality. The study is justified by the high rate of postoperative complications as a major determinant for the reduction of quality of life for the affected patients and high costs for the health system which may be reduced by individualized, perioperative hemodynamic therapy.

### Study design

This is a prospective, multi-center, international, randomized controlled clinical trial in 380 patients scheduled for major abdominal surgery in six European centers having a large number of patients eligible for study inclusion (see Appendix). The study coordination will be conducted by a team of principle investigators (PI), [name], [name], [name], and [name], from the University Medical Center Hamburg-Eppendorf, Germany and from the Rostock University Medical Center, Germany.

The trial was designed in accordance with the fundamental principles established in the Declaration of Helsinki and within the requirements established by the German legislation in the field of biomedical research, the protection of personal data, and bioethics. The study was registered in January 2017 (received on 12 January 2017) at https://clinicaltrials.gov with the identification number NCT03021525. The study was approved by the Ethics Committee Giessen, Germany in February 2017 acting as the overall Ethical Review Board for this study (Additional file 1). Further, we can specify that all participating centers will obtain the approval from the local Ethical Review Board according to individual legislation regulations. Before inclusion into the study, written informed consent from the patient will be obtained (Additional file 2). See Additional file 3 for the Standard Protocol Items: Recommendations for Interventional Trials (SPIRIT) Checklist of the study protocol and Fig 1. for the adapted SPIRIT Figure.

**Fig. 1 Fig1:**
[figure not shown]
Study flow chart. iGDT: individualized, goal-directed therapy

After an initial meeting of the principle investigators (PIs) together with all local main investigators (LMI) the centers are visited at the partner hospital and trained with regard to the process of randomization, enrollment, data acquisition, and treatment strategies.

### Study population

To be eligible for inclusion into this study (day 0), each patient must fulfill all the inclusion criteria during screening and prior to enrollment into the trial.

#### Inclusion criteria

To ensure the presence of marked surgical trauma, open visceral, urological, and gynecological surgery are covered by this study. Expected duration of surgery must be ≥ 120 min and the requirement of volume therapy must be expected to be ≥ 2 l. Risk for any postoperative complications must be ≥ 10% as assessed preoperatively by the ACS-NSQIP (American College of Surgery – National Surgical Quality Improvement Program, www.acsnsqip.org) risk calculator [4, 18, 19].

#### Exclusion criteria

Patients aged < 18 years, use of a laparoscopic approach, patients who are not in sinus rhythm, patients having highly impaired left ventricular function (ejection fraction < 30%) or severe aortic valve stenosis (aortic valve area < 1 cm^2^, mean gradient > 40 mmHg), pregnant women, emergency surgeries (surgery required within 24 h), primarily vascular surgery, patients suffering from septic shock, patients having pheochromocytoma, patients suffering from non-cardiac chest pain, patients suffering from anuric renal failure, those refusing to consent, patients receiving palliative treatment only (likely to die within 6 months) and patients suffering from acute myocardial ischemia (within 30 days before randomization) are excluded from the study. Further, in case that clinicians intended to use cardiac output monitoring for clinical reasons patients should also not be included in the study.

#### Randomization

The use of an electronic Case Report Form (eCRF) including randomization software ensures a safe and prompt randomization via computer. Participants will be centrally allocated to treatment groups (allocation ratio: 1:1) by the eCRF-generated randomization procedure (randomization in blocks of 6). This ensures a balanced allocation with respect to centers and treatment arms. The study is summarized in Fig. 1.

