#### Methods against bias

Due to the nature of the intervention, blinding to all types of staff involved in the study is not possible. Primary and secondary outcome parameters will be assessed by a local investigator, on days 1, 3, 5, 7, and on day 28, blinded to allocation. Moderate and severe complications will additionally be verified by the LMI or a designee. Source data verification will be performed by the monitors by regular on-site monitoring visits. To minimize bias provoked by learning principles of goal-directed therapy in the past, and thereby influencing control group treatment, predominately hospitals without prior regular use of cardiac output monitoring in the respective procedures were selected. Further, the inclusion of non-university centers will allow better comparison of the study group to the broad clinical reality.

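### A single, published block size of 6, apparently applied within centres in an unblinded trial, weakens allocation concealment

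*Protocol article*

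**What the plan says.** The Randomization section of the protocol article states: "Participants will be centrally allocated to treatment groups (allocation ratio: 1:1". The method is an "eCRF-generated randomization procedure (randomization in blocks of 6", and of this the article says: "This ensures a balanced allocation with respect to centers and treatment arms". The abstract (Methods/design) adds: "Eligible patients will be randomly allocated to two treatment arms within the participating centers". No second block size is mentioned.

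Under Methods against bias, "blinding to all types of staff involved in the study is not possible". The same section protects outcome assessment: "Primary and secondary outcome parameters will be assessed by a local investigator, on days 1, 3, 5, 7, and on day 28, blinded to allocation".

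Other relevant statements:
- Study design: patients are "scheduled for major abdominal surgery in six European centers".
- Documentation and data acquisition: site staff enter the patient's details in a secure web system before the arm is returned. The first two patients of each centre are taken to be one per arm.
- Inclusion and Exclusion criteria: eligibility depends partly on expected duration of surgery, expected volume requirement, and whether clinicians intend cardiac output monitoring for clinical reasons. It also requires a calculated ACS-NSQIP complication risk of at least 10%.
- Trial status: recruitment began in August 2017 and was expected to end at the close of 2018.

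**The concern.** With one fixed block size, each completed block contains exactly three patients per arm. Staff in an unblinded trial see which arm each earlier patient received. Once three patients in a block have gone to one arm, the rest of that block is determined. A recruiter who keeps count then knows the next allocation before deciding whether to enter the next patient.

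Surgery is scheduled and several entry criteria call for judgement, so there is room to hold back or bring forward a patient according to perceived risk. Such selection acts before randomization. Blinded outcome assessment does not prevent it, and the primary model (treatment, clinic and treatment slope) includes no patient risk covariate.

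**Working it through.** The article gives no predictability figure to reproduce. Its total of 380 does follow from its own inputs: 167 per group for 48% against 33% (two-sided 0.05, 80% power) gives 334, and 334 × 1.10 + 2 × 6 = 379.4.

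**Inputs.** Block of 6 at 1:1, so 3 + 3 (Randomization). Six centres (Study design). 380 patients (Sample size), so 380/6 ≈ 63 per centre if recruitment is equal (assumption).

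**Certain allocations in one block.** There are C(6,3) = 20 equally likely sequences. An allocation is certain when one arm is already used up.

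| Position | Condition | Probability |
|---|---|---|
| 1 to 3 | cannot occur | 0 |
| 4 | first three all in one arm: 2/20 | 0.10 |
| 5 | three of the first four in one arm: 2 × 4/20 | 0.40 |
| 6 | always | 1.00 |

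The sum is 1.5 per block. The closed form for a block of 2m agrees: 2m/(m + 1) = 6/4 = 1.5. The share is 1.5/6 = 25%, and 0.25 × 380 = 95.

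With 63 patients per centre there are ten full blocks and three patients over, which gives 10 × 1.5 = 15 of 63, or 23.8%. This is the figure of about 24% used for comparison below.

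**Best guess.** Always guessing the arm with more places left is right, on average, m + ½(4^m / C(2m,m) − 1) times per block: 3 + ½(64/20 − 1) = 4.1 of 6, or 68.3%, against 50% by chance.

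**If blocks ran across centres.** With one list over six equally recruiting centres, and each site seeing only its own allocations, simulation gives a certain share of about 0.1%.

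**Possible bias.** Bias = 0.25 × shift in risk between arms within the predictable quarter. The shift is an assumption; the article offers no figure.

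| Shift (points) | Bias (points) | Share of the assumed 15-point effect |
|---|---|---|
| 5 | 1.25 | 8% |
| 10 | 2.5 | 17% |
| 20 | 5 | 33% |

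**Effect of varying block sizes.** Simulation with 63 patients per centre and an observer who knows the set of sizes and tracks every allocation:

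| Sizes | Certain | Best guess right |
|---|---|---|
| 6 | 23.8% | 0.68 |
| 4, 6, 8 | 2.3% | 0.68 |
| 4, 6 | 5.4% | 0.69 |

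A larger fixed block helps little: 20% certain with size 8 and 16.7% with size 10.

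**The case against.** Five points can be made for the plan.

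- **The list is concealed.** Allocation is central and returned only after the patient's details are entered. This stands. A reader might infer that concealment fails altogether, but the article does not support that: what remains is inference from past allocations, open only to staff who track them.
- **Blocking within centres is not stated.** This stands as a condition. The claimed balance by centre, the abstract's wording and the one-per-arm run-in pair all point to centre-level blocks, but no sentence says so.
- **Sites may not know the block size.** No site-facing document is at hand, so what sites were told is unknown. The size is nevertheless in a public article that describes recruitment as continuing to the end of 2018.
- **Measured risk could be adjusted for.** A reader might infer that no later analysis could help. In fact each patient needs a preoperative ACS-NSQIP risk estimate, and baseline characteristics are to be shown by arm, so steering on measured risk could be seen and partly corrected. Selection on unmeasured factors could not.
- **Entry is not wholly discretionary.** The risk threshold and many exclusions are defined. This limits the room for steering without removing it.

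**Conclusion.** The weakness is real, but conditional. If blocks of 6 run within centres, and staff know the size and follow their centre's allocations, a quarter of allocations (about 95 of 380; about 24% with 63 patients per centre) are known in advance. If blocks run across centres, the share is negligible.

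The article gives no evidence of steering. The bias of 1.25 to 5 points follows only from assumed risk shifts of 5 to 20 points acting on every predictable allocation, so it shows scale and is not an estimate. Concealment is weakened, and the remedy is cheap enough that the change should be made.

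**What to change.** For the unused part of each centre's list, generate blocks of randomly varying size (for example 4, 6 and 8), stratified by centre, and do not disclose the sizes to sites. State explicitly that randomization is stratified by centre, since the article only implies it.

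The cost is one new list in the existing eCRF and a slightly larger possible imbalance per centre at the end of recruitment: an unfinished block of 8 can leave a difference of 4, against 3 for a block of 6. The change removes most of the certain knowledge (about 24% down to about 2%). It does not reduce better-than-chance guessing, which stays near 68%.

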## General care and procedures for the control and intervention groups

### General information on patients’ treatment

Treatment besides hemodynamic optimization in both the control and the intervention group is defined based on the respective guidelines and recommendations of the medical societies to avoid extremes of clinical practice. Oxygenation will be targeted for a SpO_2_ of 94% or higher by choosing an appropriate level of inspired oxygen. The tidal volume will be set at 6–8 ml/kg and PEEP at 0–10 cm H_2_O according to clinical needs and the decision of the physician in charge. The target for heart rate is below 100 bpm, the target range for mean arterial blood pressure is 65 mmHg or higher, using vasopressors as required. Core temperature will be maintained at > 36 C by continuous heat application to the patient and fluid warming. Choice of fluid is determined on the basis of the recent guidelines [20] for intravascular volume therapy. Arterial or venous blood samples are taken regularly for assessment of hemoglobin, oxygenation, decarboxylation, electrolytes, and lactate. An epidural catheter is placed before induction of anesthesia at the discretion of the treating anesthesiologist. Perioperative analgesia will be provided by epidural or intravenous infusion of analgesics according to the standards of the participating centers. Blood products will be transfused according to the Guidelines from the European Society of Anesthesiology (for an overview see Additional file 4: Table S1) [21].

### Treatment of the control group

Patients in the control group will be treated according to established basic treatment goals as described in the general information on patient treatment (heart rate < 100 bpm, mean arterial pressure > 65 mmHg, SpO_2_ > 94%, and core temperature > 36 C). In the control group, no specific vasopressor is prescribed to achieve the mean arterial pressure goal and the choice of drug is at the discretion of the treating anesthesiologist. Basic anesthesiological monitoring by five-lead electrocardiogram, pulse oximetry, non-invasive blood pressure monitoring and capnography is performed in every patient. Placement of an arterial and central venous line is at the discretion of the treating clinician, as is the decision to administer fluids and catecholamines. After extubation, hemodynamic treatment in the recovery room is at the discretion of the treating anesthesiologist either by administration of fluids, catecholamines, or other drugs as required.

### Treatment of the intervention group

The trial intervention period will commence from the induction of anesthesia until 8 h after surgery, or until discharge from the postoperative intensive or intermediate care unit. Drugs of choice are dobutamine for inotropic support and norepinephrine as a vasopressor. No other catecholamines should be used in the intervention group. Hemodynamic management is performed according to standard treatment until an arterial catheter is placed. The signal from the arterial catheter is then processed by non-calibrated pulse-contour analysis (ProAQT©; Pulsion Medical Systems, Feldkirchen, Germany) for pulse-pressure variation (PPV) and cardica index (CI) measurement. A fluid challenge will be performed by infusion of 500 ml in < 15 min. The choice of fluid in case of indicated fluid loading is determined on the basis of the recent guidelines for volume therapy [20].

#### Initial assessment of individually optimized CI

When arterial pulse-contour analysis is implemented, patients receive an initial hemodynamic assessment based on PPV and CI in order to identify individual values of optimal CI as shown in algorithm 1 (Fig. 2).

**Fig. 2 Fig2:**
[figure not shown]
Algorithm 1. Intervention algorithm of initial assessment of individually optimized Cardiac Index (CI). CI: Cardiac index; PPV: Pulse pressure variation

First, fluid status is optimized by fluid loading (500 ml in < 15 min) until PPV is < 12%. At least 15 min after induction of general anesthesia, after individual optimization of the fluid status, the patient’s individual optimal CI in the specific situation of general anesthesia is defined and used as the individual hemodynamic goal until the end of the intervention period. Only if this value is below 2.5 l/min/m^2^ inotropes are administered to reach this minimum CI to prevent patients from developing a low cardiac output.

#### Hemodynamic assessment during mechanical ventilation

After the initial determination of the individual optimal CI, further hemodynamic assessment during mechanical ventilation and surgery is performed every 15 min, or if mechanical ventilation is continued after surgery every 30 min, or if required due to hemodynamic instability at any time according to algorithm 2 (Fig. 3). Hemodynamic parameters are documented every 30 min during surgery and every 60 min postoperatively.

**Fig. 3 Fig3:**
[figure not shown]
Algorithm 2. Intervention algorithm during mechanical ventilation. CI: Cardiac index; PPV: Pulse pressure variation

If the CI is below the initially assessed individual optimal CI, again fluid status is evaluated based on PPV. Fluids are administered as long as PPV is higher than 12% and the CI increases. Again, inotropes are used when fluid optimization does not result in realization of the individual optimal CI. This treatment algorithm is always reassessed when the CI drops below the individually optimized CI.

#### Hemodynamic assessment after extubation (maximum 8 h after surgery)

Because of spontaneous breathing, after extubation PPV is not usable anymore for fluid status evaluation. Hemodynamic assessment is then performed according to algorithm 3 (Fig. 4). Hemodynamic assessment after extubation is repeated every 30 min, or if required due to hemodynamic instability at any time according to algorithm 3. Hemodynamic parameters are documented every 60 min.

**Fig. 4 Fig4:**
[figure not shown]
Algorithm 3. Intervention algorithm during spontaneous breathing. CI: Cardiac index; PPV: Pulse pressure variation

When the CI is below the individually determined optimal CI, a fluid challenge (500 ml in < 15 min) is performed. If the increase of CI is higher than 15%, a fluid challenge of 500 ml is repeated. If the increase of the CI is below 15%, or the CI even decreases, inotropes should be started or increased.

### Primary and secondary outcomes

#### Primary endpoint

Considering the high relevance for the individual patient and for society, the postoperative outcome is most appropriately reflected by a combination of morbidity and mortality. Therefore, the primary endpoint is a composite comprising the rate of patients with one or more moderate or severe postoperative complications or death within 28 days post surgery. Moderate and severe postoperative complications are defined by 22 single-organ outcome failures based on a consensus statement of the European Society of Anesthesiology (ESA) – European Society of Intensive Care Medicine (ESICM) joint taskforce on perioperative outcome measures [22]. A summary of the included organ failures and the severity grading is given in Additional file 5: Table S2.

